### Data collection {19}

At the time of recruitment, we will collect socio-demographics, history of illness and clinical examination. At every visit we will do systematic clinical examination, determine adherence to interventions and assessment about any complaints and any adverse events. Both allopathic and Siddha physicians will perform clinical examination and collect relevant details according to their systems.

**Baseline laboratory investigations:** (i) Haemogram; (ii) Liver function tests (LFTs); (iii) Renal function tests (RFTs); (iv) Haemoglobin A1c and blood sugar, (v) RT-PCR for SARS-CoV-2 (respiratory samples: nasopharyngeal swab, oropharyngeal swab, in addition, sputum, bronchoalveolar lavage (BAL), if available); (vi) electrolytes, (vii) Chest X-ray; (viii) Electrocardiogram (ECG) (ix) Immunoglobulins

### Data Analysis plan {20}

The analysis plan on the primary and secondary outcome is described in the below table

Table 5: Statistical analysis plan{20a}

| Outcome                                                              | Hypothesis                                 | Outcome measure                                        | Methods of analysis            |
|----------------------------------------------------------------------|--------------------------------------------|--------------------------------------------------------|--------------------------------|
| Primary                                                       |                                            |                                                        |                                |
| Viral load of SARS-CoV-2                                             | Reduction of Viral Load after intervention | Viral Load                                             | T test                         |
| Immunological markers                                                | Improvement                                | Th1, Th2 cells                                         | T test                         |
| Secondary                                                     |                                            |                                                        |                                |
| Reduction in the risk of disease progression                         | Reduction of complication                  | Incidence of complication                              | Kaplan Meier survival analysis |
| Reduction in intensive supportive care and long-term hospitalization | Reduction of complication                  | Incidence of complication                              | Kaplan Meier survival analysis |
| Clinical profile in terms of Siddha System of Medicine (SSM)         |                                            | Questionnaire                                          | Chi-square test                |
| Adverse events/effects                                               |                                            | Presence of drug related adverse event (time to event) | Kaplan Meier survival analysis |

**Data monitoring {21a}:** The data safety monitoring committee constituted by Ministry of AYUSH will be responsible for the monitoring the data

**Harms/ adverse reaction reporting {22}:** The adverse events will be documented for each patient and will be reported to Pharmacovigilance cell of Siddha Central Research Institute, Chennai

**Ethical approval {24}:** The study will be initiated after the approval of the Institutional Ethics Committee of Government Stanley Medical College, Chennai.

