## Objectives

### Primary:{7a}

- To determine efficacy of KSK compared with CZ in reducing the onset of clinical symptoms in asymptomatic patients
- To determine effectiveness of KSK compared with CZ in terms of reduction of SARS-CoV-2 viral load from the baseline
- To examine the effect of KSK compared with CZ on immune system in terms of selected immunological markers

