### Interventions Arm -1{11a}

#### **Kabasura Kudineer (Siddha Polyherbal decoction)**

Table 1: Composition of KSK

| S. No | Botanical name                 | Family         | Part Used   | Parts  |
|-------|--------------------------------|----------------|-------------|--------|
| 1.    | Zingiber officinale     | Zingiberaceae  | Rhizome     | 1 part |
| 2.    | Piper longum            | Piperaceae     | Fruit       | 1 part |
| 3.    | Syzygium aromaticum     | Myrtaceae      | Flower bud  | 1 part |
| 4.    | Anacyclus pyrethrum     | Asteraceae     | Rhizome     | 1 part |
| 5.    | Tragia involucrata      | Euphorbiaceae  | Leaves      | 1 part |
| 6.    | Solanum anguivi         | Solanaceae     | Leaves      | 1 part |
| 7.    | Terminalia chebula      | Combretaceae   | Fruit rind  | 1 part |
| 8.    | Justicia adathoda       | Acanthaceae    | Leaves      | 1 part |
| 9.    | Anisochilus carnosus    | Lamiaceae      | Whole plant | 1 part |
| 10.   | Costus speciosus        | Costaceae      | Rhizome     | 1 part |
| 11.   | Tinospora cordifolia    | Menispermaceae | Whole plant | 1 part |
| 12.   | Clerodendrum serratum   | Verbanaceae    | Leaves      | 1 part |
| 13.   | Andrographis paniculata | Acanthaceae    | Whole plant | 1 part |
| 14.   | Cyperus rotundus        | Cyperaceae     | Rhizome     | 1 part |
| 15.   | Sida acuta              | Malvaceae      | Whole plant | 1 part |

**SOP for preparation:** To 5g of KSK coarse powder, add 240 ml of water and allowed to boil till, it reduces to one-fourth (60ml) and filter the decoction (KSK).

**Dose** : 30 – 60 ml twice daily.  
**Dosage form** : Kudineer (decoction).  
**Route of administration** : Oral.  
**Time of administration** : twice a day- Morning and Night before food  
**Duration of therapy** : 14 days  
**Follow up period** : 14 days after treatment

[illegible]

|                    |  |   |   |   |   |   |   |   |   |   |   |   |   |   |   |   |
|--------------------|--|---|---|---|---|---|---|---|---|---|---|---|---|---|---|---|
| SSM principles     |  | ✓ | ✓ | ✓ | ✓ | ✓ | ✓ | ✓ | ✓ | ✓ | ✓ | ✓ | ✓ | ✓ | ✓ | ✓ |
| Laboratory Markers |  | ✓ |   |   |   |   |   | ✓ |   |   |   |   |   |   |   | ✓ |

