### Specimen labelling and processing

Personal protective equipment (apron, hand gloves, face shield, N95 Masks etc.) will be used and all biosafety precautions will be followed so as to protect individuals and the environment. Proper labelling (name/age/gender/specimen ID) will be done on specimen container and other details of sender (name/address/phone number) on the outer container by mentioning “KSK\_COVID\_trial”

[figure not shown]

Figure 1: Lab Specimen collection

Laboratory sample collection Schedule: (i) Oropharyngeal swabs (0,7,14 days) - for SARS-CoV-2 RT-PCR (samples will be transported to Laboratory, as per the guidelines); (ii) Blood sample (0,7,14 days) (iii) ECG, Xray (Base line)

All samples would be stored for future-related tests.

Table 4: Schedule of investigations

| Parameter              | D0 | D7 | D14 |
|------------------------|----|----|-----|
| Haemogram\$            | ✓  | ✓  | ✓   |
| *LFT                   | ✓  |    | ✓   |
| #RFT                   | ✓  |    | ✓   |
| HbA1c, BS              | ✓  |    |     |
| qRT- PCR for SARS Cov2 | ✓  | ✓  | ✓   |
| Electrolytes           | ✓  | ✓  | ✓   |
| Chest X-ray            | ✓  |    |     |
| ECG                    | ✓  |    | ✓   |
| Immunoglobulins        | ✓  | ✓  | ✓   |

\$Hb%, total leucocyte count and differential WBC -neutrophils, lymphocytes, eosinophils, monocytes and basophils, RBC count, platelet count; #Renal function test -BUN, Creatinine; \*Liver function test -albumin, bilirubin, ALT, AST, alkaline phosphatase. AST, aspartate transaminase; ALT, alanine aminotransferase; RBC, red blood cell; WBC, white blood cell; BUN, blood urea nitrogen; ECG, electrocardiogram; SARS-CoV-2, severe acute respiratory syndrome coronavirus 2; qRT-PCR, real-time reverse transcription-polymerase chain reaction; HbA1c, haemoglobin A1c; Hb, haemoglobin

Frequency and duration of monitoring: (i) Patients will be monitored daily until discharge from the hospital and followed up till 14 days;

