### Outcome assessment

Clinical outcomes: (i) Assessment of clinical symptoms (ii) Clinical profile of SSM (iii) Time to test COVID-19 Negative

Safety Assessment: (i) Elevation of ALT to more than five-fold upper normal limit; (ii) Anaphylaxis; and (iii) Adverse events and serious adverse events.

Laboratory outcomes: (i) Viral RNA loads and cycle threshold values in serial samples of nasopharyngeal

and oropharyngeal swabs and blood, collected every week (to document anti-viral activity). (ii) Immunoglobulins values in serial samples of serum collected every week (to document immunomodulatory effect)

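### The primary viral-load t test names no deciding visit, although RT-PCR is taken after baseline at both D7 and D14; name one visit and adjust for D0

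*Protocol*

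**What the plan says.** The second primary objective (Objectives, Primary {7a}) compares KSK with CZ "in terms of reduction of SARS-CoV-2 viral load from the baseline" and gives no day. In Table 5 (Data Analysis plan {20}), the viral-load row has the hypothesis "Reduction of Viral Load after intervention", lists viral load as the measure and a t test as the method, and names no visit.

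Sampling is set out under Specimen labelling and processing: "Oropharyngeal swabs (0,7,14 days) - for SARS-CoV-2 RT-PCR". Table 4 in the same section ticks the row "qRT- PCR for SARS Cov2" at D0, D7 and D14. Outcome assessment describes serial samples of swabs "and oropharyngeal swabs and blood, collected every week (to document anti-viral activity" and singles out no week. The intervention section gives "Duration of therapy : 14 days", so D7 falls in mid-treatment and D14 at its end.

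The Sample size section calls the study a pilot of 60 patients, 30 per group, without a calculation. The protocol states no significance level, sidedness or between-visit correlation, and it specifies no blinding.

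**The concern.** A two-sample t test compares one value per patient. Here there are two post-baseline values, and the text does not say which one decides the outcome. The visit is part of the definition of a primary endpoint, and the protocol itself fixes this analysis in a table presented as its statistical analysis plan, so the gap is not simply a detail left for another document.

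The two visits can disagree. If the infection clears by itself, both arms may be near undetectable at D14 and differ only at D7; equally, a chance difference may appear at one visit alone. Without a stated choice in an open-label trial, the visit can be picked once results are seen, and the error rate of this endpoint then exceeds that of one test. The problem would remain if viral load were the only primary outcome.

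A second, smaller point is efficiency. The D0 viral load is collected for every patient, and a plain t test does not make the best use of it.

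**Working it through.** The plan has no figure of its own to reproduce: the sample size has no inputs behind it and no error rate is stated.

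**Inputs.** From the protocol: two post-baseline visits (D7, D14) and 30 patients per arm. Assumed: two-sided 5% per test, and a correlation r between the D7 and D14 contrasts anywhere from 0 to 0.9. A value of 0.5 has a simple origin. If D0, D7 and D14 have equal variance s² and common correlation c, the two changes from baseline each have variance 2(1 − c)s² and covariance (1 − c)s², so their correlation is 0.5 whatever c is.

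**Step 1: error rate if either visit may be called primary.** With Z7 and Z14 standard normal under no effect:

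- either direction: 1 − P(|Z7| ≤ 1.96 and |Z14| ≤ 1.96)
- favouring KSK only: 1 − P(Z7 ≤ 1.96 and Z14 ≤ 1.96), taking positive as favourable

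At r = 0 these are 1 − 0.95² = 0.0975 and 1 − 0.975² = 0.0494. The other rows come from the bivariate normal distribution. The last column is a check by simulated t tests with 30 per arm (100,000 null trials per correlation).

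| r | Either direction | Favouring KSK only | Simulated t tests, either direction |
|---|---|---|---|
| 0 | 0.0975 | 0.0494 | 0.098 |
| 0.3 | 0.0951 | 0.0476 | 0.095 |
| 0.5 | 0.0907 | 0.0454 | 0.090 |
| 0.7 | 0.0835 | 0.0417 | 0.083 |
| 0.9 | 0.0704 | 0.0352 | 0.070 |

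One fixed visit gives 0.05 and 0.025. The inflation is thus 0.0704/0.05 = 1.4 to 0.0975/0.05 = 1.95 in either direction, and 0.0352/0.025 = 1.4 to 0.0494/0.025 = 2.0 for results favouring KSK.

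**Step 2: what adjusting for D0 gains at one visit.** Let c be the correlation of the D0 value with the value at the named visit, with equal variances. Relative to a t test on the end value, the standard error is:

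- t test on the end value: 1
- t test on the change: √(2(1 − c))
- ANCOVA: √(1 − c²), ignoring the small cost of estimating the slope

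| c | End value | Change | ANCOVA | ANCOVA gain over end value | ANCOVA gain over change |
|---|---|---|---|---|---|
| 0.3 | 1 | 1.183 | 0.954 | 5% | 19% |
| 0.5 | 1 | 1.000 | 0.866 | 13% | 13% |
| 0.7 | 1 | 0.775 | 0.714 | 29% | 8% |

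In this range ANCOVA is better than both t tests. At c = 0.5 the gain is 1 − 0.866, about 13%, against either.

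**The case against.** The strongest reply is that the text is less open than it looks. Therapy runs for 14 days, patients are still on treatment at D7, and so only D14 is literally after the intervention. This largely stands: D14 is the natural reading, and a reader who infers that D7 and D14 compete on equal terms goes further than the protocol allows. But the protocol does not say D14, and Outcome assessment gives the weekly samples equal standing, so the ambiguity is reduced and not removed.

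A reader might also infer that about 9% of null trials would be positive. That figure needs a two-sided 5% level, a correlation near 0.5, and results favouring CZ counted as positive. None of these is in the protocol, so only the range can be given. Nor does the text support a still higher rate of about 16%, which treats the end value and the change from baseline as both open at each visit: the objective already speaks of reduction from baseline.

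Two further points limit the finding. Part of the intervention section, where a visit schedule seems to have stood, is illegible in the copy read, so the absence of a named visit is established only for the legible text. And the study calls itself a pilot, which weakens a strict error-rate argument. It still states comparative primary objectives and a hypothesis test, so the contrast should be defined.

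Averaging D7 and D14 is a tempting cure, but a debatable one. If an effect exists only at D7, the average halves it, while at correlation 0.5 the standard error falls only to √((1 + 0.5)/2) = 0.87. The signal-to-noise ratio is then 0.5/0.87, about 0.58 of that at D7 alone. One named visit closes the gap without this trade-off.

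**Conclusion.** The point holds in a limited form. The primary viral-load row names no deciding visit; D14 is the likely intention but is not written in any legible part of the protocol. If either visit could be reported as primary, the chance of at least one significant result under no effect is about 7% to 9.75% against 5%, or about 3.5% to 5% against 2.5% when only results favouring KSK count. These figures rest on an assumed two-sided 5% level per test and correlations from 0.9 to 0; they describe what the wording permits, not what the investigators will do. If D14 is what is meant and is stated, the inflation disappears.

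Separately, a baseline-adjusted analysis is a better method than the plain t test. It has a standard error about 13% smaller at an assumed baseline correlation of 0.5 with equal variances, using data already scheduled. The change is worth making before results are known.

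**What to change.** In the viral-load row of Table 5, replace the t test with one contrast: the KSK minus CZ difference in log10 viral load at one named visit (D14 if end of treatment is what is meant), estimated by ANCOVA adjusted for the D0 value. State that this contrast alone decides the viral-load outcome, and report the other visit as secondary.

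The cost is one row of the table, with no new samples, visits or patients. The log10 scale needs a stated convention for undetectable values. The downside is that a difference seen only at the other visit can no longer be claimed as the primary result.

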**Trial sponsor {5b}: Central Council for Research in Siddha**

**Role of study sponsor and funders {5c}:**

The funds from the granting will be used in procuring the COVID-19 kits, CBA biomarker kits and laboratory consumables etc. Funders will have no role in study design; data collection, management, analysis, and interpretation of data and writing or dissemination of the final report.

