### Randomization, sequence allocation & allocation concealment{16a,b,c}

Simple randomization. All the eligible participants will be randomly assigned (in 1:1 ratio) in each arm to ensure balanced distribution between KSK and CZ arms. Randomization will be implemented by independent statistician who will not involve in data analysis. Equal numbers of cards with each arm assignment number randomly generated by computer will be placed in sequentially numbered envelopes that will be opened on patient enrolling.

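### Table 5 fixes a t test without baseline adjustment for the primary viral-load outcome, although day-0 qRT-PCR is scheduled for every patient; adjusting for it would cost nothing and usually add precision

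*Protocol*

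**What the plan says.** **Method.** Protocol, Data Analysis plan {20}, Table 5, has two primary rows, viral load and immunological markers. A t test is the method for both. The viral-load hypothesis is "Reduction of Viral Load after intervention", and the outcome measure is given only as viral load. The table names no covariate, no analysis day, and no choice between follow-up value, change score or within-arm comparison.

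**Objective.** Protocol, Objectives, Primary {7a}, does state a comparison between arms, and it refers to baseline: "To determine effectiveness of KSK compared with CZ in terms of reduction of SARS-CoV-2 viral load from the baseline".

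**Viral-load schedule.** Under Specimen labelling and processing, the plan is "Oropharyngeal swabs (0,7,14 days) - for SARS-CoV-2 RT-PCR". Table 4 ticks qRT-PCR at D0, D7 and D14, and Data collection {19} lists RT-PCR among the baseline investigations.

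**Immune markers.** Table 5 names Th1 and Th2 cells. Table 4 and the baseline list name immunoglobulins instead, and Outcome assessment refers to "Immunoglobulins values in serial samples of serum collected every week". Blood is taken on the same days ("Blood sample (0,7,14 days"), and the funding paragraph {5c} mentions "procuring the COVID-19 kits, CBA biomarker kits and laboratory consumables". No legible schedule entry names a Th1 or Th2 measurement on day 0.

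**Design.** There are 60 patients, 30 per arm, with "Simple randomization" in a 1:1 ratio. No stratification factor is given. The sample size section says that no assumptions could be made and calls the trial a pilot.

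**The concern.** The day-0 viral load is normally among the stronger predictors of later viral load, and this trial already measures it. A t test on the follow-up value leaves it out. A t test on change subtracts it in full, which over-corrects unless the baseline-outcome slope is close to 1. No stratification on viral load offers protection at the design stage, and the size is fixed, so precision can be gained only in the analysis.

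Two things are at stake. One is a wider confidence interval than the data need give. The other is a realised estimate that moves with any chance day-0 difference. With the follow-up value, the arm that starts lower looks better. With the change score, the arm that starts higher looks better through regression to the mean. Because the table does not say which test is meant, even the direction of this shift is open.

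**Working it through.** The plan has no calculation to reproduce.

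**Inputs from the protocol.** n = 30 per arm, 1:1, with day-0 viral load collected.

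**Assumed inputs.** Two-sided alpha 0.05, no dropout, equal SDs (set to 1) at day 0 and follow-up, roughly continuous values, and baseline-outcome correlation rho of 0.3, 0.5 or 0.7. The protocol gives none of these.

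**1. Chance imbalance at day 0.** The difference in baseline means has standard error sqrt(2/30) = 0.258 SD.

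- P(|difference| > 0.25 SD): z = 0.25/0.258 = 0.97, so 33%.
- P(|difference| > 0.5 SD): z = 0.5/0.258 = 1.94, so 5.3%.

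**2. How imbalance moves the estimate.** Per unit of day-0 difference, the follow-up estimate shifts by rho and the change-score estimate by rho − 1. For a one-standard-error imbalance (0.258 SD):

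| rho | Follow-up t test | Change-score t test |
|---|---|---|
| 0.3 | +0.077 SD | −0.181 SD |
| 0.5 | +0.129 SD | −0.129 SD |
| 0.7 | +0.181 SD | −0.077 SD |

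ANCOVA estimates the slope and removes this linear part.

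**3. Residual variance.** Follow-up: 1. Change: 2(1 − rho). ANCOVA: 1 − rho². Since 2(1 − rho) − (1 − rho²) = (1 − rho)² ≥ 0, ANCOVA's variance never exceeds that of either alternative, apart from a small cost for estimating the slope.

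| rho | Change | ANCOVA | Per-arm size at which a follow-up t test matches ANCOVA, 30/(1 − rho²) |
|---|---|---|---|
| 0.3 | 1.40 | 0.91 | 33 |
| 0.5 | 1.00 | 0.75 | 40 |
| 0.7 | 0.60 | 0.51 | 59 |

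**4. Power.** The reference effect is d = 0.736 SD, where the follow-up t test (58 df, noncentral t) has 80% power. The effect divided by the residual SD is d/sqrt(2(1 − rho)) for change (58 df) and d/sqrt(1 − rho²) for ANCOVA (57 df).

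| rho | Follow-up t test | Change-score t test | ANCOVA |
|---|---|---|---|
| 0.3 | 80% | 66% | 84% |
| 0.5 | 80% | 80% | 90% |
| 0.7 | 80% | 95% | 97.5% |

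A small-sample factor for estimating the slope, sqrt(1 + 1/(2n − 4)) = sqrt(1 + 1/56) on the residual SD, lowers the ANCOVA column by less than one point: 82.9%, 89.4% and 97.3%.

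**5. Low end of the range.** At rho = 0.2 the ANCOVA variance is 0.96 and its power at the same effect about 82%, a gain of under two points over the follow-up test. The change-score test then has about 60%.

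**The case against.** **The t test is not invalid.** This stands. Under randomisation its standard error already includes chance imbalance, and type I error is not inflated on average. A reader might infer from the imbalance figures that the planned analysis is biased. The protocol does not support that: what remains is lost precision, and bias only conditional on the imbalance that happens to occur. Unstratified randomisation is not an error either.

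**The baseline may already be used.** The objective speaks of "in terms of reduction of SARS-CoV-2 viral load from the baseline", so a t test on change is a natural reading, and that test uses the day-0 value. It would therefore be wrong to say that the plan certainly ignores baseline. The point survives because both between-arm readings are dominated, but the gain depends on the reading: at rho = 0.7 it is only 2.5 points over a change score, and at rho = 0.3 about 4 points over the follow-up value.

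**The size has no anchor in the document.** This also stands. No correlation, SD, effect or alpha is given, and a self-declared pilot has no power target. Outcome assessment includes time to a negative test, so many later swabs may be undetectable. With values piled at a detection limit, the 1 − rho² formula need not hold and the gain may be smaller.

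**Both primary rows.** A reader might infer that the same free adjustment is available for the immune row because immunoglobulins are scheduled at day 0. The analysed measure there is Th1 and Th2 cells, and no legible entry schedules these at day 0. Biomarker kits and day-0 blood make such a measurement possible but do not establish it.

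**Left to a SAP.** Covariates often are, and a SAP may exist. But Table 5 itself names the test, so this is a stated choice rather than a gap.

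**Conclusion.** The point holds for the primary viral-load outcome, as an improvement in efficiency and clarity and not as a fault in validity. The protocol fixes an unadjusted test, leaves open which one, and collects the one covariate that would improve it.

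The imbalance probabilities (33% and 5%) need only the planned 30 per arm and an approximately normal difference in means. The power gain rests on an assumed correlation. Over 0.3 to 0.7 it runs from about 4 to 17.5 points against a follow-up t test, and from about 18 down to 2.5 points against a change-score t test. It is close to nil against the follow-up test at a correlation of 0.2, and may be smaller than shown if many values are undetectable.

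For the immune row the same reasoning would apply, but only once the analysed marker and the schedule agree.

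**What to change.** - **Viral-load row of Table 5.** Replace the t test with a linear model comparing KSK with CZ: follow-up log10 viral load or Ct at a named day, on arm and the patient's own day-0 value. Report the adjusted mean difference with its 95% confidence interval.
- **If both D7 and D14 are used.** Fit one repeated-measures model with arm-by-visit terms and the day-0 value as covariate.
- **Supporting analysis.** The t test may stay, provided that the table says it is between arms and on which quantity.
- **Immune row.** First reconcile Table 5 (Th1 and Th2 cells) with the schedule (immunoglobulins) and confirm a day-0 measurement of the marker to be analysed. Then apply the same model.

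**Cost.** For viral load: one wording change and one degree of freedom, with no new data, visits or patients. Each analysed patient needs a day-0 value, which the schedule already requires. For the immune row, the cost depends on whether a day-0 assay of that marker is already intended.

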## Rationale: {6b}

In this context, one of the classical formulations from Siddha system of medicine is *Kabasura kudineer* (KSK) consists of 15 herbals ingredients which individually has anti-viral activity (6). Cucurbitacin B (-112.09), Cardiolipide (-111.5), Apigenin (-98.84) and Pyrethrin (-92.98) presented in the KSK were found to be effective in preventing novel corona virus binding and replication.(7) Determination of organoleptic characters, preliminary phytochemical analysis, physico- chemical analysis, TLC photo documentation and HPTLC fingerprint studies on KSK were analyzed.(8) Toxicological study on KSK showed that it is safe(9). KSK also possess anti pyretic, anti-inflammatory and anti-bacterial effect. Vitamin c and zinc supplementation(CZ) is being prescribed for the COVID19 positive asymptomatic patients admitted in isolation ward. The role of CZ in the management of COVID19 is still not clear. Therefore, we propose to compare the effect of KSK and CZ in terms of negative conversion of SARS CoV- 2 infection.

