### Sample size {14}

As there is no prior work on this research question, so no assumptions for the sample size calculation could be made. The present study will serve as a pilot trial. We intend to study 60 patients, each 30 in two groups.

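### Table 5 words the primary viral-load hypothesis as a fall after treatment with no comparator, although the objective compares KSK with CZ

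*Protocol*

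**What the plan says.** The second primary objective in the Protocol (Objectives, Primary {7a}) is comparative: "To determine effectiveness of KSK compared with CZ in terms of reduction of SARS-CoV-2 viral load from the baseline". The Rationale {6b} points the same way: "we propose to compare the effect of KSK and CZ in terms of negative conversion".

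The primary viral-load row of Table 5 (Data Analysis plan {20}) gives the hypothesis as "Reduction of Viral Load after intervention", and its measure and method cells read "Viral Load | T test". The row names no comparator. It does not say whether the test is paired or two-sample, which day is tested, or on what scale. The Outcome assessment section lists two candidate scales: "Viral RNA loads and cycle threshold values in serial samples of nasopharyngeal".

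On size, Sample size {14} says "We intend to study 60 patients, each 30 in two groups", describes the study as a pilot, and states that "no assumptions for the sample size calculation could be made". Table 4 schedules qRT-PCR on days 0, 7 and 14.

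**The concern.** The objective asks whether viral load falls more on KSK than on CZ. The hypothesis asks only whether it falls. Patients who clear the infection on their own show a fall whatever they are given, and the Protocol expects clearance, since it lists time to a negative test as a clinical outcome. An analyst who follows the row literally could run a before/after test in the KSK arm, find it significant, and report the primary hypothesis as met with no information on KSK against CZ. The Rationale calls the role of CZ unclear, so only the randomised contrast can answer the question asked.

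The unnamed scale matters on the other reading. Viral load spans orders of magnitude, so a two-sample t test on untransformed copies can be governed by a few high values and miss a large real difference.

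**Working it through.** **The Protocol's own figure.** There is nothing to reproduce: the 60 patients come with no alpha, power, effect or SD. Only the 30 per arm and the sampling days come from the document.

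**Assumptions.** Two-sided 5% level; baseline mean 6 log10; fall of 2 log10 in both arms; log10 SD *s* from 0.5 to 2.0; correlation *r* between D0 and follow-up of 0.3 to 0.7; no dropout; a detection floor of 1 log10 for the ANCOVA figures.

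**Step 1: can clearance alone meet the hypothesis as worded?** With no arm difference, for a paired t test on log10:

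- SD of change = s × √(2(1 − r)); noncentrality = fall × √30 / SD of change.
- s = 2.0, r = 0.3: SD of change = 2 × √1.4 = 2.37; noncentrality = 2 × 5.48 / 2.37 = 4.63; power about 99.4% per arm, so 0.994² = 98.8% in both arms.
- s = 2.0, r = 0.5: SD of change = 2.0; noncentrality = 5.48; power above 99.9% per arm.
- Smaller SDs give essentially 100%.
- If the fall is only 1 log10 (r = 0.5), the per-arm figure is 76-100% over the range of SDs.

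Under the same conditions the two-sample KSK-CZ test on log10 rejects in about 5% of trials, as it should.

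**Step 2: does the scale matter for a between-arm test?** For a true 1 log10 KSK benefit:

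- Two-sample t test on log10: noncentrality = (1/s) × √(30/2) = 3.87/s, which is 3.87, 2.58 and 1.94 at s = 1.0, 1.5 and 2.0. Power is about 97%, 72% and 47-48%.
- ANCOVA on log10: residual SD = s × √(1 − r²). At r = 0.5 the variance falls to 0.75 of its value, worth 1/0.75 = 1.33 times the patients.
- Untransformed copies: by simulation.

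| log10 SD | Paired test significant in both arms, no KSK effect: log10 | Same: untransformed | Between-arm t test, 1 log10 benefit: untransformed follow-up | Same: log10 | ANCOVA, log10 |
|---|---|---|---|---|---|
| 0.5 | 100% | 97% | 98% | 100% | 100% |
| 1.0 | 100% | 30-34% | 35% | 97% | 98-100% |
| 1.5 | 100% | 3-5% | 7% | 72% | 74-94% |
| 2.0 | 99-100% | 0.3-0.9% | 2% | 47% | 49-72% |

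A between-arm t test on untransformed change from baseline, the quantity closest to the objective's wording, has 0.3-4% power over the whole range of SDs, because the large D0 values swamp the follow-up difference. With no arm difference, the t test on untransformed follow-up values rejects in only about 0.4-2% of trials at SDs of 1.0 to 2.0.

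**Step 3: do the two problems occur together?** Mostly not. At SDs of 1.0 or more, the untransformed scale that weakens the KSK-CZ test also weakens the paired test that clearance would pass (table, third column). On log10, clearance passes the paired test almost always, but the between-arm power loss is absent.

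**The case against.** The best defence is that Table 5 is terse throughout. Its immunology and complication rows also omit the comparator, nowhere does it say the test is paired, and the title, Rationale and objective all describe a comparison. A sensible analyst would run a two-sample test. That makes the before/after analysis a possible reading and not a fixed plan. It does not repair the row, which states a hypothesis different from the objective it serves. Table 5 is labelled as the statistical analysis plan, so a later document that followed it would carry the mismatch forward.

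Three stronger readings are tempting and are not supported.

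- A reader might infer that skew destroys the power of the primary test. No section says untransformed copies are analysed, Ct values (a log-type scale) are also collected, and at SD 0.5 the untransformed follow-up test keeps 98% power. Scale and the handling of undetectable values are commonly settled in a separate SAP.
- A reader might quote the 99% clearance figure and the 2% power figure against one plan. They belong to different scales and different tests.
- A reader might count the lack of baseline adjustment as an error. A two-sample t test on follow-up or change is valid in a randomised trial; adjustment only adds precision.

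The pilot label is fair against any complaint about power, since none is claimed. It does not excuse a primary hypothesis that misses its objective.

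**Conclusion.** The point stands as a mismatch between the stated hypothesis and the stated objective. As worded, the hypothesis could be met in both arms with no KSK effect in about 99-100% of trials, given a 2 log10 natural fall and paired tests on log10. The scale concern is conditional: the loss of power is severe if untransformed follow-up copies are compared between arms and the log10 SD is about 1 or more, or if untransformed change is tested at any SD examined. It is nearly absent for follow-up values at SD 0.5 and does not arise on log10 or Ct. All SDs, falls, the floor, the correlations and the 1 log10 benefit are assumptions, because the Protocol gives none. That the hypothesis lacks a comparator rests on no assumption.

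**What to change.** Rewrite the viral-load row of Table 5 along these lines:

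- Hypothesis: mean log10 viral load (or Ct) differs between KSK and CZ at one pre-named scheduled day. The sponsor should choose D7 or D14; nothing in the Protocol ranks one above the other.
- Method: ANCOVA of that value on arm with the D0 value as covariate, reporting the between-arm difference with a 95% confidence interval.
- Undetectable values: set at the detection limit, with a tobit or rank-based sensitivity analysis.
- Within-arm change: descriptive only.

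The essential parts are the between-arm contrast, the named day and the named scale. The D0 adjustment is an efficiency gain from data already scheduled. The cost is analysis wording plus the sponsor's decision on the day; no extra patients, visits or samples are needed.
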